### Validity and reliability

This study uses a rigorous research design with a representative and predetermined sample. The chosen instruments were validated with high reliability and validity. In addition, the data collectors and the participants were blinded to the intervention group assignment to reduce biases in the evaluation of the effects of the intervention.

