### Study design and setting

This is a single-blinded, two-armed, randomized controlled trial, where the research assistant who is responsible for data collection is blinded but the provider is not blinded. This study is supported by two community centers of a non-governmental organization.

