### Participants and recruitment strategy and randomization

A trained community center staff member will help to generate a list of potential subjects from their membership list. Potential subjects will be called and recruited into the program if they fulfill the following inclusion criteria: (1) aged ≥18 years old, (2) have no cognitive impairment as evidenced by a score of 22 or above in the Hong Kong version of the Montreal Cognitive Assessment (18), (3) can understand and communicate in Cantonese, (4) provide care to older adults aged ≥60 at least 4 h per week for a minimum of 3 months, (5) use a smartphone, (6) know how to access the Internet, (7) commit to attending bi-weekly, 15–30 min online meetings with the program providers over the 3-month period, and (8) are willing to receive individual-specific video messages covering caregiving skills via WhatsApp. They will be excluded if they are (1) known to have serious alcohol and drug problems, (2) are unable to write and read, (3) have mental health problems, and (4) have already participated in other telecare health or social programs. When two or more potential subjects are taking care of the same older adult, only the one who has spent more time with the older adults is allowed to participate.

A trained research assistant (RA) will introduce the program and invite eligible subjects to join the program in the community centers, and obtain verbal consent upon their agreement. After collecting their baseline data, the research assistant will call the principal investigator (PI) of the research team for randomization. The PI will put the numbers generated from a software program called “Research Randomizer” into sealed envelopes (i.e., “1” = intervention group, “2” = control group). These envelopes will be opened sequentially when a call is received from the RA. In this study, the RA and the community center staff will be blinded, but the PI and the healthcare providers will not.

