### Intervention group

Each intervention group subject will receive three intervention components: (1) online nurse case management supported by a health-social partnership team, (2) individual-specific video messages covering caregiving skills sent via WhatsApp, and (3) an online information center and discussion forum via a password-protected, newly-developed caregiver website.Online nurse case management supported by a health-social partnership team

Each intervention group subject will be assigned to a nurse case manager (NCM) during the first week of the program. The NCM has extensive experience in providing care to informal caregivers and has been trained specifically for this program. She will meet with the subjects bi-weekly via Zoom. The time of the meetings will be settled with the agreement of both the NCM and the subjects. In the first Zoom consultation, the NCM will assess the caregiving needs and problems of the subjects by using a structured and validated assessment-intervention-evaluation tool: The Omaha System. The Omaha System consists of 42 problems under four domains ─ environmental, psychological, physiological, and health-related behaviors (19). The NCM will empower the subjects to set goals and develop a personalized care plan tailored to their identified caregiving needs and problems. The goals and care plan will be followed up and revised in subsequent Zoom consultation sessions. The NCM will also provide emotional support, encourage the subjects to discuss their concerns, identify perceived challenges to achieving their goals, and together with the subjects find solutions in the Zoom consultation sessions on how to tackle these barriers. When deemed necessary, based on a jointly developed protocol and the problems of the subjects, the NCM will refer the subjects to one of the health-social partnership team members, which includes social workers, traditional Chinese medicine practitioners, a physiotherapist, and a mental health nurse. The protocol indicates the roles and responsibilities of each member in the health and social team, the suggested assessment, interventions and an evaluation scheme for each member, and the arrangement and logistics of the program. A monthly conference will also be held among the team members to review the referred subjects’ condition, care plans, and goal status.Individual-specific video messages covering caregiving skills sent via WhatsApp

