In addition to online case management sessions, the NCM will send weekly, individual-specific videos of tips and reminders to the informal caregivers via WhatsApp, an interactive communication application. The subjects will receive videos that include, but are not limited to, the topics of common chronic diseases and their management, caregiving skills and techniques, available community services and resources, and self-care strategies. All of the videos originate from reliable organizations such as the Hospital Authority, Department of Health, and The Hong Kong Council of Social Service. To ensure the subject understands the content of the videos, the NCM will also teach and explain the content of the video, and answer any questions that they have during the online consultation sessions.Online information center and discussion forum accessed via a password-protected, newly-developed caregiver website

The research team will work with a technology company to design a website that incorporates two features, an online information center and a discussion forum. In the online information center, the members of the health-social team will regularly post general information to the informal caregivers that have been proven to be effective for them, such as family relationship management strategies, stress relieving techniques, and physical and mental health protection skills. In the discussion forum, the subjects can raise questions, either in the form of text, video, or both text and video to the health-social team members. To answer the questions, the team members will browse the discussion forum every 3 days at minimum. The forum can also serve as a peer-support platform where all of the caregivers in the intervention group can share their individual caring experiences, discuss commonly encountered issues, and seek emotional support from their peers. Peers with a similar background and experiences are believed to have a better understanding of their feelings and to be able to provide support to and receive consolation from each other. The website is only accessible to the health social team members and members of the intervention group, who will be given a preset password and username to log in. The subjects will also be told not to disclose the password to the others and all the information posted can be viewed by the people who is allowed to access the website.

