### Ethical considerations

Ethical approval was obtained from the Ethics Sub-committee of the study university. The RA will convey information about the program, including its potential benefits, risks, and the issue of confidentiality during subject recruitment. Each participant who agrees to participate in the program will be required to sign a consent form upon enrollment. The collected data will be accessed solely by the research assistants and no personal information will be disclosed. Such data will include the demographic data of the subjects, the outcome measures, and the user ID and password for accessing the virtual discussion forum. All data will be stored in a password-protected database.

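### The article claims that participants were blinded, which conflicts with its own design sections and cannot hold when only one arm receives the online programme

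*Protocol article*

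**What the plan says.** The protocol article describes blinding in three places.

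- **Study design and setting:** "This is a single-blinded, two-armed, randomized controlled trial". The same sentence explains the label: "the research assistant who is responsible for data collection is blinded but the provider is not blinded".
- **Participants and recruitment strategy and randomization:** "the RA and the community center staff will be blinded, but the PI and the healthcare providers will not".
- **Validity and reliability:** "the data collectors and the participants were blinded to the intervention group assignment to reduce biases". Here blinding is offered as a reason to trust the evaluation of the intervention.

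Other sections show what participants know and receive. To be eligible they must "commit to attending bi-weekly, 15–30 min online meetings with the program providers over the 3-month period" and be willing to receive caregiving videos by WhatsApp. Under Ethical considerations, "The RA will convey information about the program, including its potential benefits, risks, and the issue of confidentiality during subject recruitment". In the intervention arm a nurse case manager is assigned in the first week: "She will meet with the subjects bi-weekly via Zoom". That arm also gets weekly individual videos and a login, and "The website is only accessible to the health social team members and members of the intervention group". The control arm gets the community centres' usual services, which both arms receive. No sham or attention control is described.

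**The concern.** The validity section credits the trial with a property that the design sections do not give it. The claim bears on the outcomes directly. The primary outcome is the participant's own rating of perceived stress, and self-efficacy, depression, quality of life and caregiving burden are also answered by the participant. For such scales the person who supplies the rating is the participant. Someone who knows which arm they are in may answer differently for that reason alone, whoever asks the questions.

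A reader who relies on the validity section would therefore rate the risk of bias in outcome measurement lower than the design allows. The Limitations section does not correct this. It deals with low website use, technical problems and caregivers who cannot read or write, and does not mention participants' knowledge of their arm.

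**Working it through.** The article gives no figure for this point, so the check sets its sections side by side.

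**Step 1. Who is said to be blinded?**

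| Role | Study design and setting | Randomization section | Validity and reliability |
|---|---|---|---|
| Research assistant (data collector) | blinded | blinded | blinded |
| Centre staff | not mentioned | blinded | not mentioned |
| Providers | not blinded | not blinded | not mentioned |
| Principal investigator | not mentioned | not blinded | not mentioned |
| Participants | not mentioned | not mentioned | **blinded** |

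The three sections agree on the data collector. Only the validity section places participants among the blinded. Neither of the other two says in words that participants are unblinded, so the conflict is partly an inference. It rests on the single-blind label, which the design section ties to the research assistant, and on a list of blinded roles that leaves participants out.

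**Step 2. Could participants be blinded under this design?**

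1. Before randomization each participant has heard about the programme from the research assistant and has committed to its online meetings.
2. Baseline data are collected, and randomization follows.
3. An intervention participant is then assigned a nurse, meets her by Zoom every two weeks, receives weekly videos and is given a website login.
4. A control participant receives none of these, only the centre services open to everyone.

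Both kinds of participant can therefore compare what they agreed to with what they receive, and so learn their arm. The conclusion does not depend on whether anyone tells them their allocation.

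**Step 3. Which data are exposed?**

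Baseline (T1) responses are collected before randomization, so knowledge of the arm cannot affect them. The exposure is at T2, for one primary and four secondary outcomes (1 + 4 = 5), in all 80 planned participants as far as they reach T2.

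**Step 4. What does blinding the research assistant protect?**

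The questionnaires are administered by phone, so a research assistant who does not know the arm is less able to lead or interpret answers differently by arm. That protection is real. It does not act on the answer that an unblinded participant chooses to give.

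**The case against.** **The error is a few words in a closing paragraph.** Randomization, data collection, sample size and analysis do not depend on it, and correcting it changes no procedure or test. This stands. The point concerns a false statement and what readers will conclude from it.

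**Unblinded self-report is inherent in comparing a nurse-led programme with usual services.** This stands too. The absence of participant blinding is not the fault, and it remains after the correction. The fault is to claim blinding that the design does not provide.

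**The sentence may have meant that participants do not know their group at baseline.** The order of baseline assessment and randomization would support that. But it describes concealment before allocation. It would not blind participants during the programme or at T2, where the effect is evaluated.

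Three stronger readings are tempting, and the documents do not support them.

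- *A reader might infer that blinding protects nothing here.* The data-collector half of the sentence agrees with the design sections and can limit interviewer bias. The Ethical considerations section does include forum user names and passwords among the data that research assistants access. It does not say that the assistant making the T2 calls sees them beforehand, so it does not show that this blinding fails.
- *A reader might express the bias as a share of the planned effect.* An assumed shift of 0.1 to 0.2 SD would be 0.1/0.403 = 25% to 0.2/0.403 = 50% if the planned 0.403 is a standardized mean difference. If 0.403 is Cohen's f, the mean difference is 2 × 0.403 = 0.806 SD and the shares are about 12% and 25%. The Sample size section does not define the metric. Neither reading reproduces its 34 per group: at two-sided 0.05 and 80% power the normal approximation gives 97 and 25. The shift itself has no source in the documents, so these percentages cannot be used.
- *A reader might infer that disappointed controls would produce an apparent benefit.* This is plausible, but the documents say nothing about it.

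**Conclusion.** The concern holds for the participant half of the statement in the validity section. That half conflicts with the design and randomization sections and is unworkable under the intervention and control conditions described. It is also used to argue that bias is reduced. The T2 values of all five outcomes are open to response bias that blinding the research assistant does not remove.

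The direction and size of that bias cannot be derived from the documents. The conclusion rests on two readings of the text: that single-blinded carries the meaning which the design section gives it, and that controls receive nothing resembling the online meetings, as the control group section indicates.

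**What to change.** 1. In the validity section, delete the words that add participants to the data collectors in the blinding claim.
2. State the same thing wherever blinding is described: participants, providers and the principal investigator are unblinded, and only the research assistant and the centre staff are blinded.
3. In the Limitations section, state that the T2 outcomes are self-reported by participants who know their arm, and that this limits the conclusion about stress.

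Optionally, to protect the blinding that does exist, ask participants before the T2 call not to reveal their group, and have the research assistant record a guess of the allocation after the call. These steps protect and test the research assistant's blinding. They do not remedy the participant-blinding claim, and their absence from a condensed article is not an error.

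The cost is wording in three sections, plus one item on the T2 form if the optional step is taken. The validity claim becomes less favourable.

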## Discussion

The role of informal caregivers is pivotal in maintaining the ability of older adults to live independently in the community. However, the multiple health and social needs of these older adults have imposed a significant burden on informal caregivers. In previous studies, a great deal of effort was expended on investigating the needs of informal caregivers of older adults with chronic diseases such as stroke, dementia, and heart failure, although in none of the studies has the idea of finding ways to relieve their caregiving burden been put forward. As informal caregivers always make caregiving one of their top priorities, they end up sacrificing their personal time, resulting in isolation from their social circle or absence from work. The aim in this study is to take advantage of technology to provide telecare consultations aimed at relieving the stress levels and caring burden of these unpaid informal caregivers.

The strength of this study lies in its use of technology to maximize the benefits to time-conscious informal caregivers. Telecare is an Internet-based tool that is not restricted by the limitations of time and place. An online information center in this program allows caregivers to access the information that they need at their convenience and to decide when and where to read about the available sources. The informal caregivers do not need to join onsite community services, so they can save time and plan their own schedule, and come up with better arrangements to care for their loved one. With the implementation of telecare, informal caregivers can enjoy supporting services while staying at home.

In addition to the use of telecare, the support of the health-social partnership team is another strength of this study. Those in health-social partnerships work together for the benefit of the clients through effective communication and collaboration. A health-social team brings together healthcare knowledge and suggestions from people with expertise in different fields, so that different aspects of needs such as the physical, mental, and social needs of the informal caregivers can be covered. Operating a health-social team is not easy because good collaboration with the shared goals of different healthcare providers is required, as well as effective exchanges of information between them. The health-social partnerships may encounter various barriers, such as complex intersectoral collaboration, and a lack of shared values and effective communication (29). A great deal of effort should be put into ensuring that the health-social partnerships work in an orderly and efficient way. In view of this, the research team has developed protocols with the health-social team to guide the work of each healthcare provider so that they have an idea of what each other’s roles and responsibilities are. They will also hold regular meetings to discuss the needs of caregivers and the progress of the case, so that they can provide true interdisciplinary care to the informal caregivers.

Telecare would not only be beneficial to informal caregivers, but also to older adults and to society as a whole. Telecare enables caregivers to be well equipped with caregiving skills and knowledge, without the restrictions of place and time. This will ultimately help their care recipients to maintain their health and reduce the need to be admitted to a nursing home and/or hospital. As a result, the healthcare system can be less overstretched and healthcare costs can be brought down with decreased health service utilization among community-dwelling older adults.

### Limitations

Although this study has various strengths, there will be some challenges in its implementation. One possible challenge could be that the informal caregivers do not regularly visit the website or actively participate in the online discussion forum. To tackle this issue, every week the NCM will check the browsing data of the website and encourage the related participants to visit the website during a Zoom meeting. Second, the participants may have technical problems accessing the website or discussion forum. The research team will provide IT support to those caregivers who face such difficulties during the program period. Third, those caregivers who are not able to read or write may not be benefited from some parts of the intervention program, such as online information center and discussion forum. However, they can still enjoy the conversation with the NCM and the NCM will try to provide them the caregiving skills and techniques through sending weekly videos.

## Conclusion

Telecare seems to be a feasible approach to providing support to the informal caregivers of community-dwelling older adults. With the support of a health-social partnership team, it is expected that the benefits of telecare can be maximized. It is anticipated that this program, substantiated by evidence, can be implemented and sustained in the community to provide long-lasting support to both older adults and their informal caregivers.

## Ethics statement

The studies involving human participants were reviewed and approved by the Research Committee of the Hong Kong Polytechnic University (reference no.: HSEARS20220810001). The patients/participants provided their written informed consent to participate in this study.

